### Statistical analysis plan:

All analyses will follow the intention-to-treat (ITT) approach, supplemented by per-protocol sensitivity analyses. Descriptive statistics will summarise participant characteristics. The primary endpoint (CIN2 + detection) will be compared between arms using the proportional difference with corresponding 95% confidence intervals (CI). Non-inferiority will be concluded if the lower bound of the 95% CI for the difference (risk-stratified – cytology) is above the pre-specified non-inferiority margin (–10%). Referral rates, colposcopic yield and diagnostic performance metrics will be compared using chi-square or Fisher’s exact tests. ROC curve analysis will assess the discriminative performance of the triage methods. Logistic regression will be used to identify independent predictors of CIN2+, adjusting for age, HIV status, parity, and other covariates. Missing data will be handled using multiple imputation, assuming data are missing at random [18]. All analyses will be conducted using Stata version 18 (StataCorp LLC, Texas, USA).

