### Sample size calculation:

Sample size was calculated based on the primary objective of testing the non-inferiority of the risk-stratified algorithm compared with cytology-based triage for detecting CIN2+. Assuming a CIN2 + detection rate of 94% for cytology-based triage [14], a non-inferiority margin of 10%, a one-sided alpha of 5%, a power of 80%, and accounting for a 5% non-response or missing data rate, we estimate that n = 148 non-16/18 HPV-positive women (74 per arm) will be required to detect non-inferiority. This sample size will also provide > 80% power to detect a 20% relative reduction in unnecessary referrals (secondary endpoint) between study arms.

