### Study procedures, randomization, and blinding:

The study investigators will screen and identify eligible non-HPV16/18-positive women for the study. Eligible women will be invited to participate in the study after receiving a comprehensive explanation of its purpose, procedures, potential risks and benefits, and will provide written informed consent before enrolment. Once consent is obtained, an interviewer-administered questionnaire will be applied to obtain baseline information on sociodemographic characteristics, reproductive and sexual history, and HIV and HPV status using the electronic case report form (eCRF) on the REDCap database hosted on a secure CMUL server with audit trails and user authentication. Eligible participants will then be randomized 1:1 using a computer-generated permuted block randomization sequence (block sizes of 4–6) stratified by age (< 35 vs ≥ 35 years) and HIV status [Figure 1]. Allocation concealment will be maintained using sequentially numbered, opaque, sealed envelopes prepared and safeguarded by an independent trial statistician.

**Intervention arm (risk-stratified triage)**: Participants will undergo triage using a risk-stratified algorithm incorporating a composite of readily available clinical and demographic data, including older age ≥ 35 years, HIV seropositivity with CD4 < 200 cells/mm^3^, cigarette smoking, long-term oral contraceptive use > 5 years, and multiple hrHPV genotype infections, to identify women at the highest risk of CIN2+ [15, 16]. Women with any of these risk factors will be referred for colposcopy, while those without will undergo repeat testing at 12 months.**Control arm (cytology-based triage)**: Participants will undergo reflex cytology (Pap test) interpreted per the Bethesda 2014 classification [17]. Women with atypical squamous cells of undetermined significance (ASC-US) or higher will be referred for colposcopy; those with normal cytology will undergo repeat testing at 12 months.

Colposcopy and biopsy will be performed for all screen-positive women in both arms. Histopathologic diagnosis (CIN1, CIN2, CIN3, or carcinoma) will be confirmed by two independent pathologists blinded to group allocation. Blinding of participants and clinicians is not feasible due to the procedural nature of triage methods; however, laboratory personnel and outcome assessors (cytologists, pathologists, and data analysts) will remain blinded to group allocation.

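### Randomisation is stratified by age and HIV status, but the planned between-arm comparisons do not use the strata: valid, but it gives away precision, a little on CIN2+ and more on referrals

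*Protocol article*

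**What the plan says.** - Protocol article, Study procedures, randomization, and blinding: "Eligible participants will then be randomized 1:1 using a computer-generated permuted block randomization sequence", "stratified by age (< 35 vs ≥ 35 years) and HIV status". That makes four strata. In the same section, age 35 or over is one of the factors any one of which sends an intervention-arm woman to colposcopy. The HIV factor in the algorithm is seropositivity with a CD4 count below 200, which is narrower than the HIV stratum.
- Protocol article, Statistical analysis plan, primary endpoint: it "will be compared between arms using the proportional difference with corresponding 95% confidence intervals (CI". The rule is "Non-inferiority will be concluded if the lower bound of the 95% CI for the difference (risk-stratified – cytology) is above" the margin of -10%. Neither the weighting of the difference nor the type of interval is named.
- Same section, secondary endpoints: "Referral rates, colposcopic yield and diagnostic performance metrics will be compared using chi-square or Fisher’s exact tests".
- Same section, the only analysis that adjusts for the stratification factors: "Logistic regression will be used to identify independent predictors of CIN2+, adjusting for age, HIV status, parity, and other covariates".
- Protocol article, Sample size calculation: "Assuming a CIN2 + detection rate of 94% for cytology-based triage [14], a non-inferiority margin of 10" per cent, with "a one-sided alpha of 5%, a power of 80%, and accounting for a 5% non-response or missing data rate", giving 148 women (74 per arm).

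**The concern.** Stratified randomisation balances the arms on age group and HIV status, so differences in risk between strata no longer contribute to the true sampling error of the arm difference. A standard error computed from the pooled 2x2 table still counts that variation. The reported interval is then wider than the design requires, to the extent that the strata predict the outcome.

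Two comparisons are affected. The primary decision rests on one confidence bound against -10%, so even a small loss of width reduces the chance of meeting the rule. Referral rates bear on the trial's central hypothesis of fewer unnecessary colposcopies. There the age stratum is more than prognostic: in the intervention arm every woman aged 35 or over is referred by rule. The referral contrast therefore differs in kind between the two age groups, and a single pooled test does not show this.

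**Working it through.** **1. The plan's own figure.** Unstratified non-inferiority formula, both rates 0.94, margin 0.10, one-sided 5%, power 80%:

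n = (1.645 + 0.842)² × 2 × 0.94 × 0.06 / 0.10² = 69.7, so 70 per arm. Then 70 / 0.95 = 73.7, so 74 per arm and 148 in total.

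This reproduces the stated size. It makes no use of strata, so nothing below changes it.

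**2. Formula for the loss.** With 1:1 allocation inside each stratum, the simple and the Mantel-Haenszel-weighted differences are the same number; what differs is the variance attached to it. With n_s women per arm in stratum s, N = Σn_s, stratum rates p_s and overall rate P in each arm:

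- unstratified variance: Σ over arms of P(1 - P)/N
- stratified variance: Σ over arms of Σ n_s p_s(1 - p_s)/N²

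**3. Inputs.** N = 70 per arm comes from step 1. The 5.6% CIN2+ risk at 12 months for non-16/18 types is in the Introduction. Stratum sizes and stratum rates are assumptions. The sizes used are 13 / 2 / 47 / 8 per arm for <35 HIV-, <35 HIV+, ≥35 HIV-, ≥35 HIV+. Eligibility is 30-65 years, so the younger stratum covers only ages 30-34.

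**4. Primary endpoint, equal rates in both arms.**

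| Assumed stratum rates | Overall | Stratified / unstratified variance |
|---|---|---|
| 5.6% in all four | 5.6% | 1.00 |
| 3, 9, 4.5, 13.5% | 5.4% | 0.98 |
| 2, 12, 4, 20% | 5.7% | 0.95 |
| 3, 15, 8, 40% | 10.9% | 0.88 |

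Third row in full: P = (0.26 + 0.24 + 1.88 + 1.60)/70 = 0.0569, so P(1 - P) = 0.0536. The within-stratum mean is (0.255 + 0.211 + 1.805 + 1.280)/70 = 0.0507. The ratio is 0.0507/0.0536 = 0.95, and the 95% half-width goes from about 7.7 to 7.5 points. At the plan's assumed rate, with stratum rates of 96, 88, 95 and 85% (overall 93.8%), the ratio is 0.98.

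In 20,000 simulated trials per row, the chance that the lower bound exceeds -10% (Wald-type intervals, no true difference) moved from 74.0 to 74.4%, 75.9 to 77.3%, 73.8 to 77.0% and 50.3 to 56.1%.

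**5. Referral rates.** Assumed control rates are 30, 40, 28 and 50%. Assumed intervention rates are 25 and 40% under 35; the 100% in both ≥35 strata follows from the protocol.

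- Overall: control 21.86/70 = 31.2%, intervention 59.05/70 = 84.4%.
- Unstratified: 0.2148 + 0.1320 = 0.3467.
- Stratified: (14.69 + 2.92)/70 = 0.2515. The ≥35 strata of the intervention arm contribute nothing.
- Ratio 0.2515/0.3467 = 0.73. The half-width falls from 13.8 to 11.7 points.

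**6. Does ignoring the strata harm coverage?** Simulated coverage of nominal 95% intervals at 5-6% risk was 93.6-94.2% for the unstratified Wald interval and 93.3-93.4% for the stratified Mantel-Haenszel interval with a Wald-type standard error. For referrals they were 97.0% and 93.6%. The unstratified interval did as well or better throughout.

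**The case against.** **The article is silent, not explicit, on the primary difference.** It does not say that the difference is unstratified, and weighting and interval type are often left to a separate analysis plan. This has force. Two things remain: plain chi-square and Fisher's tests are named outright for referrals, and age and HIV status are brought in for the predictor regression but not for the arm comparisons.

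**The gain is small and rests on assumptions.** For the primary endpoint this is right. The documents give no HIV prevalence or stratum rates, and the largest gains need very strong stratum effects. Part of the simulated gain also reflects the stratified Wald-type interval being slightly too short. For referrals, a contrast as large as 31% against 84% would be decisive without stratifying; the benefit there is a narrower interval and a clearer picture by age.

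**Sparse strata.** At 5.6%, about 4 events per arm (0.056 × 74 = 4.1) would be spread over four cells, some nearly empty. This stands, and it is why a pooling rule is needed.

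**A stronger reading that does not hold.** A reader might infer that ignoring the strata gives poor interval coverage. It does not: after stratified randomisation the unstratified interval is valid and tends to be conservative when the strata are prognostic. A reader might also point to 0/74 against 3/74, where the lower limit is -8.5 points by Wald and -11.3 by Newcombe, so the conclusion flips. That comes entirely from the interval type and would occur with no strata at all. The article names neither interval.

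**Conclusion.** The mismatch is real and minor. The design stratifies by age and HIV status, and the stated comparisons do not use those strata. The consequence is lost precision, in the cautious direction for a non-inferiority claim.

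Its size, under the assumed stratum sizes and rates, is about 0-5% of variance for the primary difference near a 5.6% CIN2+ risk and up to about 12% under very strong stratum effects. For referral rates it is about a quarter (27% in the case worked). The referral figure depends on the assumed control rates and age mix, but its cause is in the protocol: age 35 or over alone triggers referral in the intervention arm. Only the age factor coincides exactly with an algorithm trigger; HIV status does so only in part.

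The few expected events are a reason to choose the interval method with care. They are not evidence for stratifying.

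**What to change.** - **Primary endpoint:** estimate the risk difference with Mantel-Haenszel weights over the age by HIV strata. Prespecify a rule for pooling sparse strata, for example collapsing to one factor, based on stratum counts and not on results by arm. Name a score-type (Miettinen-Nurminen) 95% interval because few events are expected; a stratified Wald-type interval would not cure the slight under-coverage seen at 5-6%. The stratified score interval was not itself simulated here.
- **Referral rates:** replace the plain chi-square or Fisher's test with a Cochran-Mantel-Haenszel test and a stratified difference with its interval.
- **Display:** show CIN2+ and referral differences by age stratum descriptively, since a pooled estimate averages over them.

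If a separate analysis plan already specifies this, the article's analysis section only needs to be aligned with it. The cost is analysis code and a few sentences. The strata are recorded at randomisation, the sample size does not change, and the Study Status section says that recruitment had not started, so the change can be made before any outcome data exist.

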Despite these advances, optimal triage strategies for women infected with non-HPV16/18 types remain poorly defined, particularly in LMIC settings. Most trials have focused primarily on HPV16/18-positive women, leaving the substantial population of women with non-16/18 hrHPV infections comparatively understudied [11]. This knowledge gap is particularly critical in sub-Saharan Africa, where non-16/18 types account for a larger proportion of hrHPV infections [12] and associated lesions than in high-income settings [11]. Furthermore, although cytology-based triage remains the conventional approach, it demands a robust cytopathology infrastructure and technical expertise that are often limited in resource-constrained environments. The potential of alternative, risk-stratified triage models—incorporating factors such as age, HIV serostatus, smoking history, long-term oral contraceptive use, or multiple hrHPV-type co-infections—to improve diagnostic efficiency without sacrificing sensitivity has not been systematically evaluated in these settings.

Given the high burden of cervical precancerous lesions, the logistical limitations of cytology, and the evolving landscape of HPV-based screening, there is a compelling need to identify triage strategies that are both effective and contextually feasible. This proposed non-inferiority randomized controlled trial, titled “*Risk-Stratified versus Cytology-Based Triage of Non-HPV16/18-Positive Women* (*STRAT-CIN Trial*)”, is designed to address this evidence gap. The primary objective is to determine whether a risk-stratified triage algorithm is non-inferior to standard cytology-based triage in detecting high-grade cervical intraepithelial neoplasia (CIN2+) among women positive for non-HPV16/18 high-risk types. *The central hypothesis is that, among non-HPV16/18-positive women, the risk-stratified triage approach will achieve diagnostic sensitivity comparable to cytology while reducing unnecessary colposcopy referrals*. The secondary objectives are to (1) compare referral rates, colposcopic yield, and diagnostic performance metrics between the two triage strategies, and (2) identify key clinical and demographic predictors of CIN2 + among women infected with non-HPV16/18 hrHPV types.

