### Study endpoints:

The primary endpoint is the proportion of histologically confirmed CIN2 + lesions in each study arm, and the secondary endpoints are (1) diagnostic performance metrics (sensitivity, specificity, PPV, NPV) of the risk-stratified algorithm versus cytology for CIN2 + detection; (2) referral rates for colposcopy following triage in each arm; (3) colposcopic yield, defined as the proportion of referred women with histologically confirmed CIN2+; and (4) clinical and demographic predictors of CIN2+.

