## Discussion

Persistent infection with hrHPV is the established cause of cervical cancer [6]. As a result, HPV-based screening is increasingly being adopted as the primary screening method due to its superior sensitivity relative to cytology [7, 8]. However, because HPV testing detects transient infections as well as clinically significant lesions, triage strategies for hrHPV-positive women are essential to preserve specificity and reduce unnecessary referrals. A widely adopted approach combines partial HPV genotyping—identifying HPV16/18, the types most strongly associated with cervical carcinogenesis—with reflex cytology for other high-risk types [9]. This protocol, therefore, describes a non-inferiority randomized controlled trial, titled “*Risk-Stratified versus Cytology-Based Triage of Non-HPV16/18-Positive Women* (*STRAT-CIN Trial*)”, designed to determine whether a risk-stratified triage algorithm is non-inferior to standard cytology-based triage in detecting CIN2 + among women positive for non-HPV16/18 high-risk types, and also compare referral rates, colposcopic yield, and diagnostic performance metrics between the two triage strategies in women infected with non-HPV16/18 hrHPV types. This study, therefore, introduces an innovative risk-stratified triage algorithm for women positive for non-HPV16/18 high-risk types, a population often overlooked in existing screening models. Unlike conventional cytology-based triage, which depends on resource-intensive laboratory infrastructure, the proposed algorithm will integrate easily obtainable clinical and demographic risk factors into REDCap to guide colposcopy referral decisions. By adopting a non-inferiority trial design, the study will rigorously test whether this simplified, data-driven approach can maintain diagnostic accuracy while reducing unnecessary referrals. This innovation aligns with the WHO’s call for scalable, context-appropriate screening strategies in low-resource settings [19] and has the potential to transform cervical cancer prevention in sub-Saharan Africa.

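### The central hypothesis joins kept CIN2+ detection with fewer unnecessary referrals, but the only conclusion rule uses detection, which cannot fall as referrals increase

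*Protocol article*

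**What the plan says.** The Introduction states the central hypothesis that, in the target population, "the risk-stratified triage approach will achieve diagnostic sensitivity comparable to cytology while reducing unnecessary colposcopy referrals". The Discussion says that adopting a non-inferiority design will allow a rigorous test of "whether this simplified, data-driven approach can maintain diagnostic accuracy while reducing unnecessary referrals". Both sentences join two outcomes.

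The primary objective, in the Introduction, concerns detection alone. Under Study endpoints, "The primary endpoint is the proportion of histologically confirmed CIN2 + lesions in each study arm", while "referral rates for colposcopy following triage in each arm" is the second of four secondary endpoints. The Statistical analysis plan section gives the only conclusion rule, which the Abstract repeats: "Non-inferiority will be concluded if the lower bound of the 95% CI for the difference (risk-stratified – cytology) is above the pre-specified non-inferiority margin", set at −10%. On the other outcomes it says "Referral rates, colposcopic yield and diagnostic performance metrics will be compared using chi-square or Fisher’s exact tests". It gives them no direction, threshold, order or link to the conclusion.

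On who receives histology, the section on study procedures says "Colposcopy and biopsy will be performed for all screen-positive women in both arms"; the remaining women are retested at 12 months. The Sample size calculation section adds that 148 women also give more than 80% power for a 20% relative reduction in unnecessary referrals. It states no control-arm referral rate.

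**The concern.** A non-inferiority result is useful when the new strategy offers something in return for the loss that the margin tolerates. This protocol names fewer unnecessary referrals as the main clinical return. The conclusion rule does not look at that return, and its endpoint is one that over-referral cannot harm. The trial could report non-inferiority for an algorithm that sends more women to colposcopy than cytology does, and a reader who has the Introduction and Discussion in mind could take that as support for the whole hypothesis.

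**Working it through.** **1. The endpoint and referral.** Let R = 1 if a woman is referred at triage and C = 1 if biopsy would show CIN2+. She counts as a case detected at triage only if R × C = 1, and the arm proportion is the sum of R × C divided by n. Changing one woman from R = 0 to R = 1 changes the proportion by C/n, which is 0 or 1/n and never negative. So the arm proportion cannot fall as referrals are added. It rises only when the added woman has CIN2+. This holds for any referral criterion.

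**2. The rule.** The inputs are the two CIN2+ proportions, the 95% interval and the −10-point margin. No referral quantity enters. A result that is non-inferior on detection with more referrals than cytology is therefore compatible with the rule.

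**3. The stated sample size.** With 94% in both arms, margin 0.10, one-sided 5% and 80% power:

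n = (1.645 + 0.842)² × 2 × 0.94 × 0.06 / 0.10² = 69.7, so 70 per arm; 70 / 0.95 = 73.7, so 74 per arm and 148 in total.

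The stated figure reproduces, and it is sized on detection alone.

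**4. The referral power statement.** No control rate is given, so I assume a range. For control rate p and risk-stratified rate 0.8p, with 74 per arm and two-sided 5%:

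SE = √{[p(1−p) + 0.8p(1−0.8p)] / 74}; power = Φ(0.2p / SE − 1.96).

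| Control rate p | Rate after 20% reduction | SE | 0.2p / SE | Power |
|---|---|---|---|---|
| 0.30 | 0.24 | 0.0728 | 0.82 | 0.13 |
| 0.50 | 0.40 | 0.0814 | 1.23 | 0.23 |
| 0.70 | 0.56 | 0.0785 | 1.78 | 0.43 |
| 0.80 | 0.64 | 0.0726 | 2.20 | 0.60 |
| 0.90 | 0.72 | 0.0628 | 2.87 | 0.82 |

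In this range the stated power is reached only near a 90% control rate. If the rate is unnecessary referrals per randomised woman, that means cytology refers at least nine women in ten. At p = 0.50, 80% power needs (1.96 + 0.842)² × (0.25 + 0.24) / 0.10² = 385 per arm before losses.

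**5. Can the size of the problem be read from a pass probability?** Take 5.6% CIN2+ (the 12-month figure for other high-risk types in the Introduction). Assume that the 94% is cytology's sensitivity and that colposcopy with biopsy misses nothing. Control detection is then 0.056 × 0.94 = 0.0526. Exact binomial enumeration with Wald 95% intervals and 74 per arm gives these probabilities of meeting the rule:

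- refer everyone (detection 0.056): 0.817
- detection equal to cytology (0.0526): 0.804
- refer nobody (detection 0): 0.449

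The last can be checked by hand. With no cases in the risk-stratified arm, 3 control cases give a lower limit of −0.0405 − 1.96 × 0.0229 = −0.0855, which passes; 4 give −0.0541 − 1.96 × 0.0263 = −0.1056, which fails. The probability of 3 or fewer cases among 74 at 0.0526 is 0.449.

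Referring everyone adds only 0.817 − 0.804 = 0.013 over equal detection.

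**The case against.** The strongest defence is that a single non-inferiority primary endpoint, with the offsetting benefit as a secondary endpoint, is a legitimate design. The primary objective is detection throughout. The rule says only that non-inferiority will be concluded, and if an over-referring arm finds as much CIN2+, that statement is true. Referral rate, colposcopic yield, specificity and PPV are all endpoints, so over-referral would be visible, and the order of secondary tests is often left to an analysis plan that is not shown here. Most of this stands, and it rules out several stronger readings:

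- A reader might infer that the protocol ignores referrals. It does not: they are measured, tested and given a power statement.
- A reader might infer that detection rises with every extra referral. It rises only when the added woman has CIN2+.
- A reader might infer that the protocol formally defines success as both outcomes. The pair appears as a hypothesis and in the Discussion, not as a stated criterion.
- A reader might take the 0.82 pass probability of a refer-everyone arm as the size of the fault. Equal detection passes almost as often, and an arm that detects nothing passes 45% of the time. The figure mainly reflects a 10-point margin against an event rate near 5%, which is a separate matter.

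The mismatch itself remains. The article states the hypothesis, says the design will test it, and states a rule that can test only half of it. That is a rule fixed in this document, not a detail left to another.

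**Conclusion.** The concern holds in a limited form. The detection test is a valid answer to the primary objective. It cannot by itself support the central hypothesis or the claim in the Discussion, because the endpoint cannot fall as referrals increase and no referral result enters the conclusion. This follows from who receives histology and needs no assumption about prevalence, only that a case detected at triage is one found through referral.

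The quantified part is the referral comparison. With 74 per arm, power for a 20% relative reduction runs from about 0.13 to 0.82 over assumed control rates of 30 to 90%, so the claim of more than 80% holds only near the top of that range. The figures assume 1:1 allocation, no losses, a two-sided 5% level and a normal approximation. No pass probability for the non-inferiority rule is offered as evidence of size.

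**What to change.** In the Abstract and the Statistical analysis plan section, keep non-inferiority of CIN2+ detection as the primary test. Only if it is met, test superiority for unnecessary referrals per randomised woman, defined as colposcopy referrals without histological CIN2+. The criterion is an upper 95% limit for risk-stratified minus cytology below 0. Report the total referral rate as support. State that the Introduction's hypothesis is supported only if both steps are met. If only the first is met, report that detection was non-inferior and that a reduction in referrals was not shown. Align the Discussion with this.

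In the Sample size calculation section, define an unnecessary referral and give the control rate behind the power statement, or revise the statement.

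The fixed order needs no alpha split, takes nothing from the power of the primary test, and uses data already planned, since every referred woman has histology. It leaves the referral criteria as they are. The Study Status section says that recruitment had not started at submission, so the rule can be set before any outcome is seen. The cost is that the joint claim becomes harder to make. At 148 women the second step is underpowered over most of the range above, and assuring its power could need a larger trial.

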**Methods:**

This protocol describes a two-arm, parallel, open-label, non-inferiority randomized controlled trial involving sexually active women aged 30–65 years who test positive for non-HPV16/18 high-risk HPV types during routine cervical cancer screening at the Lagos University Teaching Hospital (LUTH), Lagos, Nigeria, between June 2026 and January 2027. A total of 148 eligible women will be randomized in a 1:1 ratio to either a risk-stratified triage arm or a cytology-based triage arm. Participants in the intervention arm will be triaged using a composite algorithm incorporating age, HIV status, cigarette smoking, long-term oral contraceptive use, and multiple hrHPV genotype infections, while participants in the control arm will undergo reflex cytology according to the Bethesda 2014 classification. The primary outcome is the proportion of histologically confirmed CIN2 + lesions detected in each study arm. Secondary outcomes include diagnostic performance metrics, referral rates for colposcopy, colposcopic yield, and predictors of CIN2+. Analyses will follow the intention-to-treat principle. Differences in CIN2 + detection rates will be assessed using risk differences and corresponding 95% confidence intervals. Non-inferiority will be concluded if the lower bound of the confidence interval exceeds the pre-specified non-inferiority margin of − 10%. Logistic regression analyses will be used to identify independent predictors of CIN2+, and statistical significance will be set at P < 0.05.

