## Introduction

Cervical cancer remains a major public health threat worldwide, with over 80% of cases and deaths occurring in low- and middle-income countries (LMICs) [1]. Recent global burden estimates indicate that women in low Human Development Index (HDI) regions experience nearly three times the incidence and up to six times the mortality compared to those in high-HDI countries [2, 3]. In sub-Saharan Africa, cervical cancer is among the leading causes of female cancer mortality, often affecting women during their most productive years, thereby imposing substantial socioeconomic and familial burdens [4]. In Nigeria alone, approximately 15,000 new cases are diagnosed annually, with nearly two-thirds resulting in death [5].

Persistent infection with high-risk human papillomavirus (hrHPV) is the established cause of cervical cancer [6]. As a result, HPV-based screening is increasingly being adopted as the primary screening method due to its superior sensitivity relative to cytology (Pap smear) [7, 8]. However, because HPV testing detects transient infections as well as clinically significant lesions, triage strategies for hrHPV-positive women are essential to preserve specificity and reduce unnecessary referrals. A widely adopted approach combines partial HPV genotyping—identifying HPV16/18, the types most strongly associated with cervical carcinogenesis—with reflex cytology for other high-risk types [9]. The COMPACT (COMparison of HPV genotyping And Cytology Triage) trial, for instance, demonstrated that women infected with HPV16/18 had markedly higher absolute risks of CIN2 + compared to those harbouring other hrHPV types (19.5% vs 5.6% at 12 months, respectively) [10].

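### The −10-point margin is wider than the 5.6% CIN2+ risk the protocol quotes, so at that risk a triage rule that finds no CIN2+ lies inside the non-inferiority region and has a 21–40% chance of being declared non-inferior

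*Protocol article*

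**What the plan says.** - **Endpoint** (Study endpoints): "The primary endpoint is the proportion of histologically confirmed CIN2 + lesions in each study arm". The analysis is by intention to treat, so the denominator is the women randomised to the arm.
- **Decision rule** (Statistical analysis plan): "Non-inferiority will be concluded if the lower bound of the 95% CI for the difference (risk-stratified – cytology") "is above the pre-specified non-inferiority margin" of −10%. The Methods part of the Abstract states the same rule: "Non-inferiority will be concluded if the lower bound of the confidence interval exceeds the pre-specified non-inferiority margin" of −10%.
- **Background risk** (Introduction): for HPV16/18 against other high-risk types, an external trial found absolute CIN2+ risks of "19.5% vs 5.6% at 12 months, respectively". The 5.6% is the only absolute CIN2+ risk given for the population of this trial.
- **Planning rate** (Sample size calculation): "Assuming a CIN2 + detection rate of 94% for cytology-based triage", with a 10% margin, one-sided alpha of 5%, 80% power and 5% allowance for missing data, giving 148 women (74 per arm).
- **Verification** (Study procedures, randomization, and blinding): colposcopy and biopsy are for women positive on triage. Triage-negative women in both arms have a repeat test at 12 months.

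**The concern.** A non-inferiority margin should mark the largest loss of detection that could still be tolerated. Here the permitted loss is 10 percentage points of all randomised women, while the quoted risk suggests that only about 5.6% of them have CIN2+ to find. On those figures the permitted loss is larger than everything cytology could detect, and the margin cannot protect detection on the endpoint as defined.

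The trial's main claim would be that cytology triage can be replaced without losing CIN2+ detection, and its findings are meant to inform practice and policy. If the margin admits large losses, a declaration of non-inferiority says little about missed precancer.

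This is not a detail that can be left to an analysis plan. The endpoint, margin and rule are all stated, and no separate document could repair them without contradicting this one.

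**Working it through.** **1. The plan's own sample size.** With p = 0.94 in both arms, margin d = 0.10, one-sided alpha 5% and power 80%:

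n = (1.645 + 0.842)² × 2p(1 − p) / d² = 6.18 × 2 × 0.94 × 0.06 / 0.01 = 69.7, so 70 per arm; 70 / 0.95 = 73.7, so 74 per arm and 148 in total.

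The stated figure reproduces. At one-sided 2.5%, which is what a two-sided 95% CI implies, the same formula gives 7.85 × 0.1128 / 0.01 = 88.5, so 89; 89 / 0.95 = 93.7, so 94 per arm and 188 in total. The 148 therefore matches one-sided 5%, not the 95% CI in the decision rule.

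**2. The scale.** A control rate of 94% cannot be the proportion of all randomised women with CIN2+ if the risk is near 5.6%. It reads as a sensitivity among women with disease. On that scale 10 points is 10/94 = 11% of control detection. On the stated endpoint it is 10/5.6 = 1.8 times control detection.

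**3. Where zero detection falls.** If cytology detects 5.6% and the algorithm 0%, the true difference is −5.6 points, which is above −10. About 74 × 0.056 = 4.1 control cases are expected.

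**4. What the rule does with zero cases in the risk-stratified arm.** Wald lower limit = −x/74 − 1.96 × √[(x/74)(1 − x/74)/74], where x is the number of control cases:

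| Control cases | Wald lower 95% limit | Newcombe lower 95% limit |
|---|---|---|
| 2 | −6.4% | −9.3% |
| 3 | −8.5% | −11.3% |
| 4 | −10.6% | −13.1% |

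Non-inferiority is declared at up to 3 control cases by Wald, and at up to 2 by Newcombe. The Miettinen–Nurminen score test has the same cut-off as Newcombe.

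**5. Probability of passing at 5.6%.** For X ~ Binomial(74, 0.056), P(X = 0, 1, 2, 3) = 0.014, 0.062, 0.134, 0.190. Hence P(X ≤ 2) = 0.21 (Newcombe) and P(X ≤ 3) = 0.40 (Wald). Enumerating both arms for the other cases:

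| True detection, algorithm vs cytology | Newcombe | Wald |
|---|---|---|
| 0% vs 5.6% | 21% | 40% |
| 2.8% vs 5.6% | 46% | 64% |
| 5.6% vs 5.6% | 65% | 78% |

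With a 90% CI, matching the one-sided 5% of the sample size, zero detection passes 40% (Newcombe) to 60% (Wald) of the time.

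**6. Sensitivity to the control rate.** The protocol gives none for its site, so these are assumptions (zero detection, 74 per arm, 95% CI):

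| Control detection | Newcombe | Wald |
|---|---|---|
| 3% | 62% | 82% |
| 5.3% (= 5.6% × 94%) | 25% | 45% |
| 5.6% | 21% | 40% |
| 8% | 6% | 15% |
| 10% | 2% | 5% |
| 15% | 0.1% | 0.3% |

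**The case against.** **The rule acts on the confidence limit.** A reader might infer that an algorithm detecting nothing simply counts as non-inferior, or that the rule accepts total loss of detection. The document does not support that. The result nearest to expectation, 0/74 against 4/74, gives a Wald lower limit of −10.6% and fails. At 5.6% such an algorithm fails 60% (Wald) to 79% (Newcombe) of the time. This stands, and the point is limited to the probabilities above.

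**The 5.6% is borrowed.** It is a background figure from an external trial and is never adopted as the expected control rate. The site is a referral centre, women with HIV are eligible, and the Introduction says non-16/18 types account for a larger share of lesions in sub-Saharan Africa. A higher rate is plausible, and the zero-detection problem fades at about 10% or more. This also stands. But the protocol offers no higher figure, and a higher rate does not make the margin sound: at 10% it equals the whole of control detection, and at 15% it still allows a true loss of 10/15 = 67%.

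**The margin may have been meant for sensitivity.** The central hypothesis speaks of sensitivity, and 94% with a 10-point margin is coherent on that scale. This explains the error but does not rescue the rule. Sensitivity needs the number of diseased women in each arm, and triage-negative women are not biopsied. The 12-month repeat test is not described as supplying histology for all of them.

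**Zero detection is a stress test.** The algorithm refers every woman aged 35 or over in a 30–65 population, so near-zero detection is unlikely. That is fair. The more telling comparison is that a rule missing half of CIN2+ passes 46–64% of the time, against 65–78% for a truly equal one.

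**Conclusion.** The concern holds in this form. The −10-point margin is applied to a proportion of all randomised women and is wider than the only absolute CIN2+ risk the protocol quotes for them. At 5.6% control detection, zero detection lies inside the non-inferiority region and is declared non-inferior 21–40% of the time. A sound margin would hold the error for an unacceptable rule near the nominal 2.5%. The nominal level is not breached in the formal sense; the fault is that the margin places total loss among the acceptable outcomes.

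The probabilities assume 74 evaluable women per arm, independent binomial counts, the 95% CI rule, and Newcombe or Wald limits, since the article names no method. They depend strongly on the assumed control rate, from 62–82% at 3% to under 1% at 15%. The root cause, a margin and control rate set on a sensitivity scale and applied to a per-arm proportion, does not depend on that rate. It needs correcting before enrolment.

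**What to change.** Amend the Abstract, Study endpoints, Sample size calculation and Statistical analysis plan together; changing the margin alone would leave the 94% calculation in contradiction.

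1. Put the endpoint, assumed control rate and margin on one scale. For the endpoint as stated, that is the proportion of randomised women with CIN2+ detected, with an expected control value and its source.
2. Replace −10 points with a margin tied to that value: a lower limit on the ratio of detection proportions, or an absolute margin that is a stated and justified fraction of it.
3. Withdraw the 80% power claim for 148 women, or restate it on that scale.
4. Use one alpha. One-sided 5% and a two-sided 95% CI do not match.
5. If 148 women cannot support the new margin, report the risk difference and detection ratio with 95% CIs, and claim non-inferiority only if the new margin is met.

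The cost is protocol and registry wording; Study Status says recruitment had not begun at submission. No procedures are added. The downside is real: the trial will probably be unable to claim non-inferiority. As an illustration only, a margin of half of 5.6% (2.8 points) at one-sided 2.5% and 80% power would need 7.85 × 2 × 0.056 × 0.944 / 0.028² ≈ 1,059 women per arm before drop-out.
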